## 3. STUDY DESIGN

This study has been developed in collaboration with stakeholders, as part of the Zorgevaluatie & Gepast Gebruik (ZE&GG) program. The stakeholders include clinicians, general practitioners, physiotherapists, patient representatives, epidemiologists, a cost-effectiveness expert, health insurers, guideline developers, and implementation experts. During a co-creation phase, multiple meetings were held in which the diverse interests and expertise of these stakeholders were integrated into the study design. Their continued involvement will guide the study's progress and implementation throughout the project.

This is a hybrid effectiveness (de-)implementation trial type II (17), with a stepped-wedge cluster trial design. A total of 10 hospitals will transition from a period with RFU to a period with COD, with a wash-out period (transition) of 2 months. The aim is to gradually de-implement RFU, with all centers eventually using COD as the standard of care. The inclusion period will last 14 months, followed by a 2-year follow-up for each patient. The total duration of data collection will be from July 2025 (first patient inclusion) to August 2028 (last patient, last visit).

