### **4.4 Sample size calculation**

We carefully considered the number of patients needed to obtain reliable estimates of the outcomes with the co-creating stakeholders and also asked orthopaedic surgeons for their opinion of convincing evidence. The agreed sample size is 250 patients per group. To provide a rough indication of the statistical power, we used the online power calculator tool available on Sealed Envelope (18). If there is truly no difference between COD and RFU, 190 patients (per intervention group) are required to be 90% sure that the lower limit of a one-sided 97.5% confidence interval will be above the non-inferiority limit of 3 on the PROMIS score with a standard deviation of 9. Anticipating 20-25% loss to follow up, we will include 250 patients per study intervention group (RFU and COD), thus a total of 500 THA and 500 TKA patients.

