## **5. TREATMENT OF RESEARCH PARTICIPANTS**

Routine Follow Up (RFU): X-ray and clinical visit following THA and TKA guidelines within

standard care: within 3 months and at 1 year after surgery. Patients are welcome to contact a HCP (i.e. general practitioner, physical therapist or hospital) in case of pain, concerns or other symptoms associated with their prosthesis at any time. RFU after THA and TKA is part of the guidelines “Totale heupprothese” and “Totale knieprothese” (5,6).

Check-Up on Demand (COD): final clinical visit with X-ray within 3 months and instructions how and when to contact a HCP. Further check-ups are scheduled only on demand (COD) by the patient or HCP. Patients are welcome to contact a HCP (i.e. general practitioner, physical therapist or hospital) in case of pain, concerns or other symptoms at any time (similar to current standard care).

In clinical practice, there is already variability in how follow-up after total hip or knee arthroplasty is conducted. Both RFU and variations of COD are utilized across different hospitals, with the choice of approach sometimes varying between individual orthopedic surgeons. The Dutch Orthopaedic Association (NOV) has confirmed that the interventions evaluated in this study are considered part of standard care.

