## **8.3 Study procedures**

Patients scheduled for total THA or TKA will be invited to participate in the study prior to their surgery. This timing ensures that participation is not influenced by the surgery itself, and a patient's potential preference for follow-up care.

Information on patient background will be collected to explore potential differences in follow-up needs, including among patients with different ethnic backgrounds. Previous research shows that people with a migrant background visit specialists and hospitals less often than

native Dutch patients with similar health and SES (19). Acknowledging the sensitivity of this topic, a 'prefer not to say' option is provided.

If the center where the patient undergoes surgery is in RFU phase, follow-up visits will be scheduled within 3 months and 1 year postoperatively. If the center is in the COD phase, patients will receive instructions during their 3-month follow-up on when and how to contact a HCP in case of concerns or complaints. In the COD phase, no standard 1-year follow-up visit will be scheduled.

Participants will be followed up to 2 years after surgery, i.e. 1 year after RFU or COD. The primary outcome, costs and the EQ-5D-5L will be measured pre-operative, at 1 year after surgery and at 15, 18 and 24 months after surgery. The other outcomes will be measured pre-operative (baseline) and at 1 year and 2 years after surgery (endpoint). Figure 1 depicts a flowchart of study participation.

[figure not shown]

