### **10.1 Primary study parameter(s)**

PROMIS physical function will be presented as mean with standard deviation, assuming normality. Differences in PROMIS physical function between the RFU and COD groups will be compared using linear mixed models, with repeated measurements clustered within participants and participants clustered within hospitals (random intercepts). The intervention group (RFU vs. COD), baseline PROMIS physical function, and time points (12, 15, 18 and 24) will be included as fixed effects to determine the crude effect of the intervention at each time point, with the primary outcome at 24 months. Given the stepped wedge design, the duration of the intervention period differs between sites. Therefore “period” is also included as a fixed effect. To assess of the effect of COD might increase over a longer period of time, an interaction term (period \* intervention) will be tested for these possible time effects for the primary outcome.

For healthcare consumption, the percentage of patients who have had at least one clinical visit or X-ray 1 year after RFU or COD will be presented for each group. Additionally, the average number of visits and X-rays per patient will be reported.

A logistic generalized linear mixed model (GLMM) will be used to compare the presence or absence of visits/X-rays (yes/no per patient) between RFU and COD. A Poisson regression analysis will be performed to assess the average number of visits and X-rays per patient, adjusting for potential confounders. Interaction terms between the confounders and the intervention group will also be included to explore whether certain patient characteristics influence the differences in healthcare consumption between RFU and COD.

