### **10.2 Secondary study parameter(s)**

For complications, surgical interventions, and additional healthcare consumption, the percentage of patients who have experienced each will be presented for each group.

Additionally, the total number of complications, interventions, and additional healthcare consumption per patient will be reported. Logistic GLMM will be used to compare the presence or absence of complications, surgical interventions, and additional healthcare consumption (yes/no per patient) between RFU and COD. A Poisson regression analysis will be performed to assess the total number of complications, interventions, and additional healthcare consumption per patient, adjusting for potential confounders.

Quality of life (EQ-5D-5L) and pain (NPRS) will be analysed using mixed models, with repeated measures clustered within participants and participants within hospitals (random intercepts). Intervention group (RFU vs. active COD vs. passive COD), baseline score, and time (15, 18 and 24 months) are included as fixed effects. Satisfaction (NSRS) will be analyzed using independent t test to compare the mean difference between the RFU and COD group.

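### The shared EQ-5D-5L and pain model uses a three-level group factor the trial does not define, and lists months at which pain is not collected

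*Protocol*

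**What the plan says.** Section 10.2 gives the two outcomes a single specification. "Quality of life (EQ-5D-5L) and pain (NPRS) will be analysed using mixed models, with repeated measures clustered within participants and participants within hospitals (random intercepts"), and the next sentence sets the fixed effects: "Intervention group (RFU vs. active COD vs. passive COD), baseline score, and time (15, 18 and 24 months) are included as fixed effects".

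Elsewhere the protocol has two conditions:

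- Design (section 3): "A total of 10 hospitals will transition from a period with RFU to a period with COD". The Table 1 legend shows the same two.
- Sample size (section 4.4): "we will include 250 patients per study intervention group (RFU and COD), thus a total of 500 THA and 500 TKA patients".
- Treatment (section 5): COD is one strategy. "Further check-ups are scheduled only on demand (COD) by the patient or HCP".
- Allocation (section 8.2): centres start on RFU and move to COD.
- Primary model (section 10.1): "The intervention group (RFU vs. COD), baseline PROMIS physical function, and time points (12, 15, 18 and 24) will be included as fixed effects".
- The other comparisons in section 10.2, including satisfaction, are RFU against COD.

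On timing, section 8.3 separates two sets of outcomes. For the first: "The primary outcome, costs and the EQ-5D-5L will be measured pre-operative, at 1 year after surgery and at 15, 18 and 24 months after surgery". For the rest, which include NPRS: "The other outcomes will be measured pre-operative (baseline) and at 1 year and 2 years after surgery (endpoint"). Table 2 agrees: the NPRS row is marked before surgery, at 1 year and at 24 months, and is blank at 15 and 18 months.

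**The concern.** A prespecified model should be one that an analyst can build from the data the trial will hold. This one fails for pain on two counts and for quality of life on one.

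The group factor has a level for which the protocol gives no rule of membership. Following the text would mean inventing a division of the COD patients. If that division were made after allocation, the comparison with RFU would risk no longer being the allocated one. The documents do not say how the division would be made.

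For pain, the listed months and the collected months overlap at one point only, so a repeated-measures model has nothing repeated to work on.

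Quality of life and pain are both named in the secondary objective (section 2). They are among the outcomes that would show whether dropping the 1-year visit costs patients anything. If the model is repaired only at analysis, both the grouping and the months would be chosen when results may already be visible.

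**Working it through.** **The plan's own figure.** The only sample-size calculation is for PROMIS (section 4.4): margin 3, SD 9, true difference 0, one-sided 2.5%, power 90%.

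n per group = 2 × 9² × (1.960 + 1.282)² / 3² = 18 × 10.51 ≈ 189.1, rounded up to 190. This reproduces the stated 190. Inflation for loss gives 190/0.80 = 238 and 190/0.75 = 254; 250 corresponds to 24% loss (1 − 190/250). Nothing below depends on these numbers. They show that the calculation rests on two groups and on a different outcome.

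**Step 1: match modelled months to collected months.**

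| Outcome | Follow-up months collected (8.3, Table 2) | Months in model (10.2) | Usable | Collected but unused |
|---|---|---|---|---|
| EQ-5D-5L | 12, 15, 18, 24 | 15, 18, 24 | 15, 18, 24 | 12 |
| NPRS | 12, 24 | 15, 18, 24 | 24 | 12 |

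For NPRS, 2 of 3 modelled months are empty, and 1 of 2 collected follow-up values is unused.

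**Step 2: fixed effects.** The design matrix has an intercept, group indicators, baseline score and time indicators. It was built for 500 simulated patients in the two groups that exist, so the third group level is empty. Full rank means every coefficient can be estimated.

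| Model | Columns | Rank |
|---|---|---|
| NPRS as written (3 groups; only month 24 has data) | 1 + 2 + 1 + 2 = 6 | 3 |
| NPRS, 2 groups, listed months | 1 + 1 + 1 + 2 = 5 | 3 |
| EQ-5D-5L as written (3 groups) | 1 + 2 + 1 + 2 = 6 | 5 |
| EQ-5D-5L, 2 groups, listed months | 1 + 1 + 1 + 2 = 5 | 5 |
| NPRS, 2 groups, months 12 and 24 | 1 + 1 + 1 + 1 = 4 | 4 |
| EQ-5D-5L, 2 groups, months 12, 15, 18 and 24 | 1 + 1 + 1 + 3 = 6 | 6 |

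For NPRS with every row at month 24, the 18-month indicator is all zeros and the 24-month indicator equals the intercept. Time adds nothing, and correcting the groups alone does not repair it. For EQ-5D-5L the single missing rank comes from the empty third group and disappears with two groups.

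**Step 3: random effects for NPRS.** Write σ_u² for the participant variance and σ_e² for the residual variance. With one follow-up value per patient, the within-hospital variance of that value is σ_u² + σ_e². Only the sum is identified. With values at 12 and 24 months, the covariance of a patient's two values within hospital is σ_u², so the components separate.

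**The case against.** The strongest reply is that the intended comparison is plain. Every other analysis is RFU against COD, including satisfaction in the same paragraph, so the three-level label reads as a drafting slip. These are secondary outcomes, and no data collection, sample size or primary conclusion changes. A 24-month pain contrast adjusted for baseline and hospital could still be obtained by dropping the empty levels and the redundant participant intercept. All of this stands, and it limits the weight of the point. It does not remove it: those repairs depart from the written model, and the text states the analysis wrongly rather than leaving detail to a statistical analysis plan.

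Stronger readings that a reader might infer, but that the protocol does not support:

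- *The split sorts COD patients by symptoms.* No definition is given. Section 5 notes that forms of COD already differ between hospitals, so a provider-level meaning is equally open. The documents support undefined, not symptom-driven.
- *No COD-versus-RFU effect could be recovered.* If two COD levels covered all COD patients, a weighted combination of them would give one.
- *Precision falls by a known amount.* No split sizes are stated. Taking 250 RFU patients and an assumed COD subset of m, and ignoring loss and clustering, the variance ratio against the full comparison is (1/m + 1/250)/(2/250). That is 1.125 at m = 200 and 3.0 at m = 50, so no single figure is justified.
- *Leaving 12 months out of the EQ-5D-5L model is an error.* The strategies diverge at the 1-year visit, and 15, 18 and 24 months match the cost questionnaires (section 10.3). Modelling only later times is defensible. It is an unexplained difference from the PROMIS model, no more.

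**Conclusion.** The point holds in two parts. First, the group factor in section 10.2 cannot be built as written for EQ-5D-5L or NPRS, because active and passive COD are undefined and contradict the two-condition design. Second, for NPRS only, two of the three modelled months have no data and the collected 1-year value is unused. The time effect and participant random intercept therefore cannot be estimated.

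It would go too far to say that both models fail on timing: EQ-5D-5L has data at every listed month and can be fitted once the factor is RFU versus COD. Nor is pain wholly unanalysable, since the 24-month value is collected.

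The ranks assume that the third group level is empty, which is what the design implies. The timing result for NPRS does not need that assumption. No numerical bias or loss of power is claimed. The consequence is that two outcomes named in the secondary objective lack a prespecified model that can be run as written. The PROMIS analysis and the sample size are unaffected.

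**What to change.** Reconcile sections 8.3 and 10.2 and Table 2, before outcome data are analysed:

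1. Replace the three-level factor by RFU versus COD as allocated, for both outcomes.
2. Give each outcome its own months. For NPRS use 12 and 24 months and report the 24-month contrast; a month-specific contrast needs a group-by-month term.
3. For EQ-5D-5L, either add 12 months to match the PROMIS model or state in one sentence why it is left out.
4. As a consistency step, carry over the period fixed effect that section 10.1 includes because of the stepped wedge; section 10.2 does not list it for these outcomes.

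The cost is protocol wording only. It needs no additional questionnaires, patients or visits, and leaves the sample size as it is.

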### **10.3 Cost-effectiveness**

The trial-based economic evaluations will focus on the primary outcome (PROMIS physical function) and QALYs, following the intention-to-treat principle. Two perspectives will be considered: 1) healthcare and 2) societal. QALYs will be calculated by multiplying utility values (based on EQ-5D-5L and valued using the Dutch tariff) by health state durations (22,23). Resource utilization will be assessed via cost questionnaires (15, 18 and 24 months after surgery) and valued according to the “Dutch manual of costing” (24). Missing data will be handled with multivariate imputation by chained equations (25). Societal costs include healthcare, absenteeism, presenteeism, unpaid productivity, and informal care; healthcare costs cover only the formal Dutch healthcare sector. Linear mixed models will estimate cost and effect differences, accounting for clustering (e.g., hospital level). Incremental cost-effectiveness ratios (ICERs) will be calculated as cost differences divided by effect differences, with uncertainty assessed through non-parametric bootstrapping nested within multiple imputation. Results will be visualized in cost-effectiveness planes and acceptability curves (26,27). Sensitivity analyses, including complete-case analysis, will test result robustness (23). The budget impact analysis (BIA) will use ZonMw’s BIA tool, based on Dutch incidence data. Perspectives include societal, government (Budget Kader Zorg), and insurer. Scenarios include: 1) RFU-only implementation, 2) COD for all patients, and 3) COD for specific subgroups (e.g., low-complication risk), defined by study results. Costs will be valued using Dutch standard costs, tariffs set by the Dutch Healthcare Authority (NZA), or average insurer tariffs. The cost-effectiveness and BIA analyses will adhere to the 'Dutch guideline for economic evaluations in health care' (28).

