### 10.4 Other study parameters

The additional study parameters, including patient characteristics, surgical characteristics, and postoperative characteristics, will be used to describe the study population and adjust for potential confounders. These variables will help account for potential baseline differences between groups, allowing for more accurate estimation of intervention effects. Patient characteristics, surgical characteristics, and postoperative characteristics will be presented as means and standard deviations for continuous variables, and frequencies and percentages for dichotomous variables. These characteristics will be used to describe the study population and adjust for potential confounders in the analysis. Including these variables in the model will help control for baseline differences between groups, thereby reducing bias and leading to more accurate and reliable estimates of the intervention effects.

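### Section 10.3 names neither baseline utility nor period in the QALY model (nor period in the cost model), although pre-operative EQ-5D-5L is collected and arm is strongly confounded with calendar time

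*Protocol*

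**What the plan says.** Section 10.3 gives the model for both halves of the ICER as "Linear mixed models will estimate cost and effect differences, accounting for clustering (e.g., hospital level"). No fixed effect other than the implied arm contrast is named. The effect measure is defined there too: "QALYs will be calculated by multiplying utility values (based on EQ-5D-5L and valued using the Dutch tariff) by health state durations". Neither the start and end of the QALY period nor the rule between measurements is given.

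The neighbouring sections do name their covariates. For PROMIS, section 10.1 has "baseline PROMIS physical function, and time points (12, 15, 18 and 24) will be included as fixed effects", and adds period as a fixed effect because of the stepped-wedge design. For EQ-5D-5L as a clinical outcome, section 10.2 has "baseline score, and time (15, 18 and 24 months) are included as fixed effects". It does not name period.

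Section 10.4 announces general adjustment for patient, surgical and postoperative characteristics: "These variables will help account for potential baseline differences between groups, allowing for more accurate estimation of intervention effects". The examples in section 8.1.3 (age, BMI, ASA score and so on) include neither baseline utility nor period.

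On timing, section 8.3 says: "The primary outcome, costs and the EQ-5D-5L will be measured pre-operative, at 1 year after surgery and at 15, 18 and 24 months after surgery". Table 2 agrees for EQ-5D-5L but shows costs at 15, 18 and 24 months only. Section 10.3 also has "Resource utilization will be assessed via cost questionnaires (15, 18 and 24 months after surgery").

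**The concern.** The same instrument is adjusted for its baseline when analysed as a clinical outcome but, as written, not when it becomes the QALY. Patients are not individually randomised; only the order in which hospitals cross over is. The RFU patients are mostly the early recruits and the COD patients mostly the late ones. A random hospital effect does not remove a drift over calendar time in case mix, utility or cost.

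Utility is not measured between surgery and 12 months. If the first year counts towards the QALY, the value recorded with a painful joint before surgery takes a large share of it, although follow-up policy cannot have affected that value. The sample size argument assumes no true difference in PROMIS. If the QALY difference is also near zero, the ICER denominator is small and sensitive to modest shifts. Cost-effectiveness is part of the trial's stated objective.

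**Working it through.** **Group size.** Section 4.4 gives margin 3, SD 9, one-sided 2.5% and 90% power. n = 2 × 9² × (1.960 + 1.282)² / 3² = 189.1, so 190 per arm, as stated. Then 190 / 0.76 = 250, a 24% loss, within the stated 20-25%. The figure does not concern QALYs; it supplies the 190 to 250 per arm, per joint, used below.

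**Overlap of the arms, from Table 1 (both joints).**

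| Months | RFU | COD |
|---|---|---|
| Jul-Dec 2025 | 440 | 0 |
| Jan 2026 | 40 (centres 7-10) | 20 (centres 1-2) |
| Feb 2026 | 20 (centres 9-10) | 40 (centres 1-4) |
| Mar-Aug 2026 | 0 | 440 |
| Total | 500 | 500 |

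Both arms recruit in the same month for 60 + 60 = 120 of 1000 patients. The other 880 are recruited in months with one arm only. The note to Table 1 splits each month equally between THA and TKA, so each separate analysis has 60 of 500.

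**Weight of the pre-operative utility** (linear interpolation over months 0, 12, 15, 18 and 24, in utility-years).

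| Window | Pre-op | 12 | 15 | 18 | 24 | Sum |
|---|---|---|---|---|---|---|
| 0-12 | 0.50 | 0.50 | – | – | – | 1.00 |
| 0-24 | 0.50 | 0.625 | 0.25 | 0.375 | 0.25 | 2.00 |
| 12-24 | 0 | 0.125 | 0.25 | 0.375 | 0.25 | 1.00 |

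From surgery, the pre-operative value is half of year 1 and a quarter of two years.

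**Chance baseline difference.** The protocol gives no utility SD, so 0.15 to 0.30 is assumed. SE = SD × √(2/n), ignoring clustering and period.
- Low: 0.15 × √(2/250) = 0.0134, times 0.5 = 0.007 QALY.
- High: 0.30 × √(2/190) = 0.0308, times 0.5 = 0.015 QALY.

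Correlation between baseline and follow-up adds to this. With assumed follow-up SD s_f of 0.15-0.20, pre-operative SD s_b of 0.15-0.30 and baseline correlation r of 0.2-0.5, the expected shift per unit of baseline difference is:
- 0-24 months: 0.5 + 1.5·r·s_f/s_b, from 0.65 to 1.50;
- 12-24 months: r·s_f/s_b, from 0.10 to 0.67.

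**Precision gained by adding baseline utility** (correlation among follow-up values assumed 0.7).
- 0-24 months: unadjusted variance 0.25·s_b² + 1.5·r·s_b·s_f + 1.771875·s_f², where 1.771875 = 0.7 × 1.5² + 0.3 × 0.65625; adjusted variance s_f²(1.771875 − 2.25·r²). At s_b = 0.15, s_f = 0.20, r = 0.2: 0.0855 falls to 0.0673, an 11% lower SE. At s_b = 0.30, s_f = 0.15, r = 0.5: 0.0961 falls to 0.0272, a 47% lower SE.
- 12-24 months: R² = r² / (0.7 + 0.3 × 0.28125) = r² / 0.784. At r = 0.2, 1 − √(1 − 0.051) = 2.6%. At r = 0.5, 1 − √(1 − 0.319) = 17.5%.

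**The case against.** The strongest reply is that section 10.3 is silent on covariates rather than ruling them out. An economic model's covariate list is commonly left to an analysis plan, and section 12.1 mentions a statistical analysis plan that is not shown. Section 10.4 also promises adjustment for baseline differences. It is true that nothing in 10.3 excludes baseline utility, and a reader should not infer that the protocol has decided against it. But 10.1 and 10.2 do name their baseline covariates, 10.3 specifies its model without them, and the characteristics cited in 10.4 do not fill the gap.

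Three stronger readings are tempting but unsupported.
- A reader might infer that the pre-operative value dominates the first-year QALY. With linear interpolation its weight equals that of the 12-month value. A full year of weight would need a carry-forward rule that the protocol does not state.
- A reader might infer that chance imbalance biases the ICER. It is imprecision, and the planned bootstrap reflects it. If the true QALY difference is near zero, the sign of the estimate is largely chance even after adjustment. Bias would need a systematic difference over calendar time, which the design permits but the protocol does not show.
- A reader might infer that costs and QALYs certainly cover different periods. They would if QALYs run from surgery and costs from month 12, but the window is unstated. Section 8.3 also lists costs pre-operatively and at 1 year, and section 8.1.3 collects healthcare use during the first year.

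It also stands that every hospital contributes to both arms and that consecutive patients are approached before surgery, which limits selection.

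**Conclusion.** The point holds as an improvement to a specified model, not as a demonstrated error in a result. Followed as written, 10.3 leaves the QALY contrast without the baseline covariate used for the same instrument in 10.2, and both economic contrasts without the period term used in 10.1. This is a design in which 880 of 1000 patients are recruited in single-arm months.

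The size depends on the window. From surgery, half of any baseline gap enters mechanically, about 0.007 to 0.015 QALY for a one-SD chance difference, and adjustment lowers the SE by about 11% to 47%. Over months 12 to 24 there is no mechanical effect and the SE falls by only about 2.6% to 17.5%. These figures rest on assumed SDs and correlations and on individual-level standard errors without clustering or period effects. The overlap count and the interpolation weights do not depend on the SDs or correlations.

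**What to change.** In section 10.3:
- add baseline EQ-5D-5L utility and period as fixed effects in the QALY model, and period in the cost model, consistent with 10.1;
- state the window and compute costs and QALYs over that same window for the main ICER, with from-surgery QALYs as a sensitivity analysis;
- reconcile the cost time points in section 8.3 with Table 2 and section 10.3.

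This takes a few sentences and no extra data, since pre-operative EQ-5D-5L and inclusion date are already recorded. The downside is that adjusting for period widens the interval, as it already does for PROMIS in 10.1. By how much cannot be computed from the protocol, which gives no intracluster correlation.
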